## Treatment

### Surgical methods

1. Microscopy group

A surgical microscope (5x–15x) is set in the surgical field in order to perform the following procedures: With the diameter of the donor’s bile duct as well as alignment in mind, either the recipient’s left and right bile ducts or common bile ducts are selected as anastomosis points. Interrupted suture with an absorbent suture is performed to suture the back and front of the bile duct walls (size 6–0). All ligations shall be tied outside. A tube is placed in the anastomosis site.

2. Surgical loupe group

Wear a surgical loupe (2.5x–4.5x), which is also used in normal surgery, and perform the following procedures: Set it in the surgical field. With the diameter of the donor’s bile duct as well as alignment in mind, either the recipient’s left and right bile ducts or common bile ducts are selected as anastomosis points. Interrupted suture with an absorbent suture is performed to suture the back and front of the bile duct walls (size 6–0). All ligations shall be tied outside. A tube is placed in the anastomosis part.

## Data collection

This study examines and collects information in accordance with the following schedule. The blood test and abdominal contrast-enhanced CT do not include anything special and is conducted to collect information as in regular medical care.

### Items to collect in the study

Patient background: gender, age, BMI, primary disease, liver function prior to surgery, surgical historyFactors of surgery: Completion rate of biliary reconstruction using a surgical microscope, duration of surgery, length of time required for biliary reconstructionBlood test: hepatic biliary enzymes (AST, ALT, ALP, γGTP), bilirubin (total bilirubin, direct bilirubin) (***Table 1***)Regarding complications: presence of biliary complications: bile leakage (diagnose by drainage and puncture), anastomotic biliary stricture (cases in which treatment such as endoscopic biliary tube insertion or percutaneous cholangiodrainage was required)Cholangiographyn (direct imaging, MRCP): evaluate the presence of anastomotic stricture and the presence of anastomotic leakage (***Table 1***).Abdominal contrast-enhanced CT: evaluate the presence of intrahepatic bile duct dilatation (***Table 1***).

**Table 1 T1:** Items to collect in the study.

ITEM	PRIOR TO SURGERY	FOLLOWING SURGERY	OBSERVATION PERIOD FOLLOWING SURGERY			UPON DISCONTINUATION

Period	0–4 Weeks before	0 weeks	12 weeks following surgery	24 weeks following surgery	52 weeks following surgery	Upon discontinuation

Medical checkup	○	—	○	○	○	○

Obtainment of consent	○	—	—	—	—	—

Random allocation	•	—	—	—	—	—

Patient background	○	—	—	—	—	—

Factors of surgery (total duration of surgery, length of time required for biliary reconstruction)	—	○	—	—	—	—

Blood test (hepatic biliary enzymes, bilirubin)	○	—	○	○	○	○

Regarding complications	—	—	○	○	○	○

Biliary form evaluation (direct imaging or MRCP)	—	—	○			

Abdominal contrast-enhanced CT	○	—	○	○	○	○

To be conducted upon obtaining consent.

Regarding the postoperative observation period, each evaluation date shall be within the acceptable range of ± 28 days.

## Statistical analysis

The estimated sample size is 158 (79 in each group). As a difference to be detected, the incidence of biliary complications by the conventional method was set to 25%, while the incidence by microscope was set to 10% (the effective rate was calculated as 75% and 90%). The number of cases required was calculated by setting the α error on one side as 5% and the detecting power as 80%. Regarding the biliary reconstruction under a microscope, we will use the Chi-square test to examine whether or not there is a statistically significant difference between the microscopy and the surgical loupe group. The significance level is set to be 5%. When a statistically significant difference is observed between the two, we will determine that biliary reconstructions under a microscope is effective. Exploratory analysis will be conducted for the secondary outcomes.

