## Study design

It is an open-label randomized controlled study in which target patients who meet the registration requirements are randomly allocated to a surgical loupe group and a microscopy group after obtaining their consent (Ratio 1:1).

The procedures used in this study are as follows: A graft from a living donor is transplanted once the liver of the recipient is completely removed. Revascularization is performed followed by biliary reconstruction. The presence of biliary complications is morphologically evaluated by cholangiography under fluoroscopy or magnetic resonance cholangio-pancreatography (MRCP). In addition, computed tomography and postoperative blood tests (increase in liver enzymes and biliary enzymes) are used for evaluation.

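### The trial is sized with a one-sided 5% error, but the primary chi-square test states no side or direction; run as an ordinary two-sided test at 5%, it has about 70% power, not 80%

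*Protocol article*

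**What the plan says.** All of the relevant text is in one paragraph of the protocol article, under Statistical analysis.

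- Size: "The estimated sample size is 158 (79 in each group").
- Planning rates: "the incidence of biliary complications by the conventional method was set to 25" per cent, "while the incidence by microscope was set to 10" per cent.
- Error and power used for the sizing: "The number of cases required was calculated by setting the α error on one side as 5% and the detecting power as 80" per cent.
- Primary test: "we will use the Chi-square test to examine whether or not there is a statistically significant difference" between the two groups.
- Level of that test: "The significance level is set to be 5" per cent.
- Success rule: "When a statistically significant difference is observed between the two, we will determine that biliary reconstructions under a microscope is effective".

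A side is mentioned once, in the sizing sentence. The sentences on the test, its level and the success rule mention neither a side nor a direction. Allocation is 1:1 (Study design).

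**The concern.** The number of patients and the primary test should rest on the same error rate. Here the number rests on a one-sided 5% error, while the test is described in the terms of an ordinary chi-square test. That statistic squares the difference between the two proportions, so comparing it with its usual 5% critical value rejects for a difference in either direction, which is a two-sided 5% test. An analyst who follows the paragraph with default software would run that test.

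Two things are at stake. The first is power: the two-sided test needs a larger difference to reach significance, so the chance of missing the planned effect exceeds the 20% that the plan accepts. The second is the decision on the only confirmatory comparison, since secondary outcomes are exploratory. Some plausible results succeed at one-sided 5% and fail at two-sided 5%. The chance of wrongly declaring the microscope better when the two methods are equal is also about 5% under one reading and about 2.5% under the other. In addition, the success rule does not require the difference to favour the microscope.

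**Working it through.** **Inputs** (Statistical analysis, Study design): loupe rate p1 = 0.25, microscope rate p2 = 0.10, difference d = 0.15, n = 79 per group, 1:1 allocation, α = 0.05, target power 0.80. Assumption: no continuity correction, because that is what reproduces the plan's figure.

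**Formula.** Pooled-variance comparison of two proportions, with p̄ = (0.25 + 0.10)/2 = 0.175:

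n = [z_α √(2p̄(1 − p̄)) + z_β √(p1(1 − p1) + p2(1 − p2))]² / d²

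- √(2 × 0.175 × 0.825) = √0.28875 = 0.5374
- √(0.1875 + 0.0900) = √0.2775 = 0.5268
- z_β = 0.8416 for 80% power

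**Step 1: reproduce the plan's figure (one-sided 5%, z_α = 1.645).**
n = (1.645 × 0.5374 + 0.8416 × 0.5268)² / 0.0225 = (0.8839 + 0.4433)² / 0.0225 = 78.3, so 79 per group and 158 in total. This matches the plan exactly.

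**Step 2: the same calculation at two-sided 5% (z_α = 1.960).**
n = (1.0532 + 0.4433)² / 0.0225 = 99.5, so 100 per group and 200 in total.

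**Step 3: power with 79 per group.**
Power = Φ[(d√n − z_α × 0.5374) / 0.5268], with d√n = 0.15 × 8.888 = 1.3332.

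| Test at 5% | Argument of Φ | Power (formula) | Power (exact enumeration, uncorrected chi-square) |
|---|---|---|---|
| One-sided | (1.3332 − 0.8839)/0.5268 = 0.853 | 80.3% | 81.3% |
| Two-sided | (1.3332 − 1.0532)/0.5268 = 0.532 | 70.2% | 72.2% |

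By the formula, the chance of missing the planned effect rises from about 20% to about 30%.

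**Step 4: the effect for which 158 patients give 80% power at two-sided 5%.**
Take p2 = 0.085, so d = 0.165 and p̄ = 0.1675. The two roots are √0.27889 = 0.5281 and √0.265275 = 0.5150. Power = Φ[(0.165 × 8.888 − 1.960 × 0.5281)/0.5150] = Φ(0.838), about 80%. The microscope rate would have to be about 8.5%, not 10%.

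**Step 5: a result on which the side decides.** With 79 per group and 8 events in the microscope group:

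- 16 loupe events: pooled rate 24/158 = 0.1519, z = (8/79)/√(0.1519 × 0.8481 × 2/79) = 0.1013/0.0571 = 1.77. One-sided p = 0.038, two-sided p = 0.076.
- 17 loupe events: pooled rate 25/158 = 0.1582, z = 0.1139/0.0581 = 1.96. Two-sided p = 0.0498.

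So 16 against 8 is a success one-sided and a failure two-sided.

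**Step 6: direction of the success rule.** Under the two-sided test, a significant result in favour of the loupe has a probability of about 2.5% if the methods do not differ, and about 0.000004 at the planning rates. The rule as worded would count such a result as efficacy.

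**The case against.** The strongest reply is that the plan never calls the final test two-sided. The only side mentioned is one-sided, and the 5% level of the test follows soon after as the same percentage, so it can be read as the same one-sided 5%. For a 2×2 table the chi-square statistic is the square of the two-proportion z statistic, so a signed one-sided version exists and naming the chi-square test does not exclude it. The aim is directional throughout: the Objective, Expected results and planning rates all look for fewer complications with the microscope. Under that reading power is 80.3%, and the success rule is sound, because a one-sided test can be significant only in the microscope's favour.

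Much of this stands. A reader might infer that the true power is 70%; the document supports that only under the ordinary reading of the test. A reader might also infer that 158 is miscalculated, but it is right for its stated inputs. Nor does anything in the document suggest that the side will be chosen after the data are seen.

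What does not stand is that the paragraph settles the matter. It attaches the side to the sizing alone, words the test as one for a difference, and mentions neither a signed statistic nor a halved p-value. The statistical analysis plan, not shown here, may name the side. A two-sided one would contradict the published power, and a one-sided one would still leave this paragraph in need of the missing words.

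**Conclusion.** The point holds in conditional form. The sample size is correct for one-sided 5%, and the described analysis does not carry that side over. Run as an ordinary chi-square test at two-sided 5%, the trial has 70.2% power for 25% against 10% (72.2% exact), about 10 percentage points below the stated figure. Run as a signed one-sided 5% test, it has the stated 80%. The missing direction in the success rule is a defect under the ordinary test only.

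These figures assume the planning rates, 79 analysed patients per group and no continuity correction. The difference between the one-sided and two-sided results does not come from the approximation, since exact enumeration shows it too. This is a mismatch between sizing and test, not an arithmetic error, and it does not show that the trial must recruit 200 patients. It still needs settling before outcome data are seen, because it governs the primary decision.

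**What to change.** Make the sizing and the test use one error rate, keep 158 patients, and do so before outcome data are seen. Either option works:

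- (a) State that the primary chi-square test is two-sided at 5%, and restate the power as about 70% for 25% against 10%, or about 80% for 25% against 8.5%.
- (b) State that the primary test is the signed, one-sided 5% version of the chi-square test, for fewer complications with the microscope. The 80% power then stands.

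Under either option, add that efficacy is claimed only if the complication rate is lower in the microscope group.

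The cost is a few words in the Statistical analysis section and no extra patients. Option (a) publishes a less favourable power. Option (b) keeps the power but accepts about a 5%, rather than 2.5%, chance of a false claim in the microscope's favour, and the text should say so.

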## Discussion

Biliary complication is more frequent in living donor liver transplantation than deceased donor liver transplantation [5,6,7]. Biliary complication is associated with outcomes of liver transplantation in terms of graft function and quality of life. For anastomotic stricture, an endoscopic approach and percutaneous transhepatic cholangiodrainage (PTCD) are required after surgery, and hepaticojejunostomy may be performed in some cases [9]. Endoscopic management of biliary stricture is technically more challenging in LDLT than in DDLT, because of the complexity of the biliary anastomosis including multiple anastomosis, tortuous and angulated biliary anatomy. Even after the successful endoscopic approach, multiple stent exchange to prevent stent occlusion is needed. In also patients with PTCD, multiple exchange of drainage tube is usually needed. Since quality of life is often disturbed in patients with biliary stricture despite the development of postoperative intervention, prevention of biliary complication is highly important.

For preventing biliary complications, various ideas have been implemented from a surgical point of view. For example, the ischemia to the bile duct stumps, the number and size of bile ducts has been reported as causes of biliary complication. The efficacy of minimal hilar dissection to preserve maximal vascular integrity of the bile duct in recipient surgery [5]. With respect to the number of bile ducts in the graft, we have been performing intraoperative cholangiography with radiopaque filament encircling bile duct to detect the appropriate cut point [10].

As one of the important innovations, biliary reconstruction with a microsurgical technique [11]. This approach has the technical advantage of enhanced visualization of the operative field including biliary reconstruction for conspicuously small bile duct [11]. The technique is considered effective to prevent physical trauma to the bile duct epithelium and conduct more precise placement of stitches during the biliary anastomosis.

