According to the report about results of routine microsurgical biliary reconstruction by Lin et al., the incidence of biliary complication significantly decreased compared to the previous reports. In other reports, Yan et al. concluded that microsurgical technique and fixed operator could decrease the biliary complications of LDLT [12]. Favorable outcomes of microsurgical biliary reconstruction have been reported based on single-center experiences.

In the current multi-facility randomized trial, we made a protocol to clarify its efficacy as well as its versatility. To evaluate the responsibility of surgical microscope on postoperative biliary complication, we set type of graft, primary disease of the recipient, facility as allocation factors in this randomized study. All facilities participating in this study have sufficient experiences of living donor liver surgery and microsurgery.

If this study reveals the efficacy and versatility of biliary tract reconstruction with a microscope, it will be one of the options for improving outcomes of biliary reconstruction in living-donor liver transplantation.

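### Allocation is minimised on graft type, primary disease and facility, but the deciding chi-square test ignores all three; if they are prognostic, the test is mildly conservative and gives up some power

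*Protocol article*

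**What the plan says.** The Registration section of the protocol article specifies minimisation with three allocation factors: graft side, the recipient's primary disease and the facility. The Discussion gives the reason. To assess the microscope's part in postoperative biliary complication, "we set type of graft, primary disease of the recipient, facility as allocation factors in this randomized study".

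The Statistical analysis section then fixes the confirmatory step: "we will use the Chi-square test to examine whether or not there is a statistically significant difference" between the microscopy and loupe groups. If the difference is significant, "we will determine that biliary reconstructions under a microscope is effective". No stratum or covariate is named for this test, and no stratified or adjusted analysis of the primary endpoint appears elsewhere in the article.

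**The concern.** Minimisation holds the arms nearly equal on the three factors, so the part of the outcome variation that they explain can hardly contribute to a chance difference between arms. The plain chi-square test computes its variance as though allocation had been simple, and still counts that part. When the factors matter, its standard error is too large for the design actually used.

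Two things follow. The true type I error falls below the nominal 5%, and some of the precision bought by the allocation scheme is not used. With few events expected, that precision is worth keeping if it costs nothing. The adjusted analysis should also be fixed in advance because the trial is open-label: covariates chosen once outcomes are known would be open to challenge.

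**Working it through.** **Inputs from the protocol article.** Event rates of 25% (loupe) and 10% (microscope); 79 per group, 158 in total; 1:1 minimisation on three factors; three facilities; sample size found by "setting the α error on one side as 5% and the detecting power as 80"%; for the test, "The significance level is set to be 5"% with no side stated.

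**The plan's own figure.** Pooled-variance formula without continuity correction, mean rate (0.25 + 0.10)/2 = 0.175:

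n = [1.645·√(2·0.175·0.825) + 0.842·√(0.25·0.75 + 0.10·0.90)]² / 0.15²
= [1.645·0.5374 + 0.842·0.5268]² / 0.0225 ≈ 78.3, rounded up to 79 per group, 158 in total.

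The stated figure is reproduced. One-sided power at 79 per group is 80.3%.

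**Why the test is conservative.** Let R² be the share of outcome variance explained by the factors. With the factors balanced, the true variance of the difference is about (1 − R²) times the chi-square variance, so

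true two-sided size ≈ 2·[1 − Φ(1.96/√(1 − R²))].

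With R² = 0 this is 5%. Reading it backwards, R² = 1 − (1.96/z)², where z is the critical value for the true size:

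- 4.6%: z = 1.995, R² ≈ 3.5%
- 3.9%: z = 2.064, R² ≈ 10%
- 3.5%: z = 2.108, R² ≈ 14%

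**Simulation.** The article gives no prognostic strength, so the odds ratio (OR) per factor is an assumption and is varied. Set-up: N = 158, biased-coin minimisation, two-sided 5%; chi-square test against an ordinary linear risk-difference model adjusted for the three factors.

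| Assumed OR per factor | Chi-square size | Power gain from adjusting (points) |
|---|---|---|
| 1 | 5.1% | −0.6 |
| 2 | 4.6% | 0.9 |
| 3 | 3.9% | 2.4 |
| 4 | 3.5% | 4.0 |

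The adjusted model's size was 4.9–5.1%.

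A separate run used 40,000 trials per setting, factors with 2, 4 and 3 levels, a biased coin of 0.8, and the OR taken between extreme levels:

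| Assumed OR | Chi-square size, two-sided | Two-sided power, chi-square vs adjusted | One-sided power, chi-square vs adjusted |
|---|---|---|---|
| 2 | 4.7% | 72.0 vs 72.4 | 81.4 vs 82.0 |
| 3 | 4.4% | 72.5 vs 74.2 | 82.1 vs 83.5 |
| 4 | 3.7% | 72.5 vs 75.5 | 82.5 vs 84.5 |
| 6 | 3.1% | 73.3 vs 77.7 | 82.8 vs 85.9 |

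At OR 1.5 the chi-square size was 5.1%, so nothing measurable was lost. Deterministic minimisation gave nearly the same results.

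**Does the adjusted method hold its size?** Expected events: 79 × 0.25 + 79 × 0.10 = 19.75 + 7.90 ≈ 28. With factors of 2, 3 and 3 levels, the model has 1 + 2 + 2 + 1 (arm) = 6 parameters beyond the intercept. Under deterministic minimisation (3,000 trials, simulation error about 0.4 points), two-sided results at OR 2 and OR 3 were:

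- Logistic standardisation with a delta-method standard error: size 6.4% and 6.4%.
- Linear model with a small-sample-corrected (HC3) standard error: size 5.4% and 5.1%; power 71.7% and 74.8%, against 72.6% and 74.5% for chi-square.

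The choice of variance method therefore matters as much as the decision to adjust.

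**The case against.** **The effect is conditional.** The article never says how strongly the three factors predict complications. The causes its Discussion names are others: blood supply to the duct stumps, and "the number and size of bile ducts has been reported as causes of biliary complication". This stands. Choosing the factors with biliary complication in view suggests a belief that they matter, but does not quantify it.

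**The gain is small and depends on the method.** With HC3 standard errors there was essentially no power gain at OR 2 to 3, and the delta-method logistic version would replace a conservative test with a liberal one. This also stands, and it limits which remedy can be recommended.

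**An unseen analysis plan may adjust.** It may, and effect estimates and supportive analyses are properly left to it. But the protocol is not silent: it names the deciding test and the decision rule. An adjusted primary analysis would change that stated test, so the protocol wording would still need to follow.

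**Stronger readings that the documents do not support.** A reader might infer that the trial misses its planned power. In every re-run setting the one-sided power of the chi-square test was 81.2% or more, against the planned 80%. The lower two-sided power comes from a different question, the unstated side of the test, and lends no weight here. A reader might also infer that the analysis should adjust for duct size or duct plasty. The Discussion does not name duct plasty as a cause. Table 1 places allocation before surgery, and the trial is open-label, so whether to perform duct plasty is decided after allocation with the arm known. Adjusting for it could introduce bias.

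**Conclusion.** The mismatch between allocation and primary test is real, but its consequence is modest and conditional. For assumed odds ratios of 2 to 4 per factor, the two-sided size of the chi-square test falls to roughly 4.6% down to 3.5%. The power given up against a model-based linear adjustment is about 0.4–0.9 points at OR 2, 1.7–2.4 at OR 3 and 3.0–4.0 at OR 4, across the two runs. With weak factors (OR 1.5 or below) there is no practical loss.

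The error runs in the conservative direction. A significant result from the planned test would not be undermined by this point, and the sample size of 158 is not invalidated. The figures rest on the assumed odds ratios, the assumed number and frequency of disease classes, and the plan's own 25% and 10%. The change is worth making because it is nearly free, not because the planned analysis would mislead.

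**What to change.** In the Statistical analysis section, replace the deciding test with a comparison adjusted for graft type, facility and primary disease, and state:

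- the grouping of primary disease into two or three classes, fixed in advance;
- the estimator and its variance. One option is a linear risk-difference model with model-based or small-sample-corrected standard errors. Another is a re-randomisation test that replays the actual minimisation algorithm. A logistic standardised estimate with a plain delta-method standard error should not be used without showing that it holds its size with about 28 events;
- that the adjusted risk difference is reported with its confidence interval;
- that the unadjusted chi-square test is kept as a sensitivity analysis.

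The decision rule should then refer to the adjusted analysis. The cost is wording, settled before outcomes are examined: the three factors are already needed at registration to run the minimisation, so no extra patients or data items are required. A re-randomisation test would also need the registration order and the exact minimisation settings to be kept.

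### The success rule names no direction: a trial sized one-sided is judged by a non-directional chi-square test, and any significant difference counts as efficacy

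*Protocol article*

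**What the plan says.** Everything relevant stands in one paragraph, the Statistical analysis section of the protocol article.

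- **Planned effect.** It has a direction: "the incidence of biliary complications by the conventional method was set to 25%, while the incidence by microscope was set to 10" per cent. The paragraph restates these rates as 75% and 90% of patients treated effectively.
- **Sample size.** It is one-sided: "The number of cases required was calculated by setting the α error on one side as 5% and the detecting power as 80" per cent. The result is 158 patients, 79 per group.
- **Test.** It has no direction. A chi-square is to show "whether or not there is a statistically significant difference between the microscopy and the surgical loupe group", at a level of 5% with no mention of one or two sides.
- **Conclusion rule.** "When a statistically significant difference is observed between the two, we will determine that biliary reconstructions under a microscope is effective".

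The primary endpoint (Endpoints section) is the incidence of Clavien-Dindo class III or higher biliary complications within 52 weeks, so a lower value is better. No other section adds a direction to the conclusion rule.

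**The concern.** The last sentence of the rule turns the test result into the trial's conclusion, and it is the only success criterion the article gives. It asks whether the arms differ and does not ask which arm did better. For a 2×2 table the chi-square statistic is unchanged when the arms are swapped, so the test does not supply the missing condition either. Applied word for word, the rule gives the same verdict for significantly fewer and for significantly more leaks and strictures under the microscope.

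A prespecified rule should give the right conclusion without the reader adding a condition. This one also leaves open what would be concluded if the microscope did significantly worse. The gap is tied to a second one: the one-sided alpha appears only in the sample size sentence and is not carried into the sentences on the test and its level. Whether the design has its stated power depends on how that is settled.

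**Working it through.** **Inputs** (all from Statistical analysis, except the allocation ratio, which is in Study design): loupe rate p₁ = 0.25; microscope rate p₂ = 0.10; alpha 5% one-sided for the sample size; power 80%; 79 per group; 1:1 allocation. Assumption: chi-square without continuity correction, because this reproduces the stated sample size.

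**1. The plan's own sample size.** With pooled variance, p̄ = (0.25 + 0.10)/2 = 0.175:

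n = [z_α √(2p̄(1−p̄)) + z_β √(p₁(1−p₁) + p₂(1−p₂))]² / (p₁ − p₂)²

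Here √(2 × 0.175 × 0.825) = 0.5374, √(0.1875 + 0.0900) = 0.5268, z_β = 0.8416 and (0.15)² = 0.0225.

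- One-sided 5% (z_α = 1.6449): (0.8839 + 0.4434)² / 0.0225 = 78.3, rounded up to **79 per group**. This is the stated figure.
- Two-sided 5% (z_α = 1.9600): (1.0532 + 0.4434)² / 0.0225 = 99.5, rounded up to **100 per group**, 200 in total.

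By this formula the stated size is that of a one-sided test in favour of the microscope.

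**2. Power at 79 per group, 25% against 10%.** Power = Φ{[0.15 √79 − z_α × 0.5374] / 0.5268}.

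| Test | Formula | Exact binomial enumeration |
|---|---|---|
| One-sided 5% | Φ(0.853) = 80.3% | 81.3% |
| Two-sided 5% | Φ(0.532) = 70.2% | 72.2% |

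**3. Does the chi-square separate benefit from harm?** Take 14/79 with a complication in the loupe group and 25/79 in the microscopy group. The pooled proportion is 39/158 = 0.2468. The standard error is √(0.2468 × 0.7532 × 2/79) = 0.0686. The difference is 11/79 = 0.1392, so z = 2.03 and chi-square = 4.12, above 3.84. Swapping the arms gives the same 4.12 and, under the rule, the same verdict. With a continuity correction z falls to (10/79)/0.0686 = 1.85, which is not significant at two-sided 5%, so this example is borderline.

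**4. How often would a significant result point the wrong way?** The product of two binomial(79) distributions was summed over all tables with |z| ≥ 1.96 and more complications under the microscope (uncorrected, two-sided 5%, loupe rate 25%):

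| True microscope rate | Significant, microscope worse |
|---|---|
| 10% (planned) | below 0.0001 |
| 25% (no effect) | 2.6% |
| 30% (assumed) | 10.6% |
| 35% (assumed) | 28.1% |
| 40% (assumed) | 53.0% |

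The rates from 30% to 40% are illustrations and do not come from the article.

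**5. Link to sidedness.** A truly one-sided test in the planned direction cannot be significant when the microscope does worse, so it would close the gap by itself. If one-sided 5% were instead applied by comparing the chi-square with 2.706 (1.645²) while the rule stayed as worded, the wrong-direction chance with both rates at 25% would be 5.0%.

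**6. Cost of adding a direction.** Only tables with more complications under the microscope stop counting as success. At the planned rates these have a probability below 0.0001, so essentially no power is lost.

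**The case against.** The strongest reply is that the direction is already there. The same paragraph defines the difference to be detected as 25% against 10%, ties effectiveness to being free of complications (75% and 90%), and sets a one-sided alpha. The Background, Expected results and Discussion sections all describe fewer complications as the aim. In that setting the rule is naturally read as referring to that difference. If the test is run one-sided, as the sample size assumes, an excess under the microscope could not be significant at all.

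Most of this stands. A reader might infer that the sponsor would report significant harm as efficacy, but the documents do not support that. It would take investigators who saw more leaks and strictures under the microscope and still called it effective, against their own stated hypothesis. The larger percentages in the table rest on assumed microscope rates of 30% to 40% and on a two-sided test that the article does not specify. They give the chance of a significant excess, not the chance that anyone would misreport it.

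A reader might also infer that the fault is wholly separate from the sidedness of the test. It is not, because an explicit one-sided test would remove it.

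What the reply does not remove is the wording. The rule is stated and not merely left out, it names no direction, and the sentences on test and level do not carry the one-sided alpha forward.

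**Conclusion.** The point holds as a modest correction. The trial is planned with a direction, but its analysis sentences and success rule have none. Taken literally, a significant excess of complications under the microscope meets the criterion for effectiveness. The intended direction is clear from the paragraph, and at the planned rates the wrong-direction chance is negligible.

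The larger numerical consequence lies in the unstated sidedness: about 80% power at 79 per group if the test is one-sided 5%, about 70% (formula) to 72% (exact) if it is two-sided 5%. These figures assume an uncorrected chi-square and 79 evaluable patients in each arm.

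**What to change.** Replace the rule with wording such as: *Biliary reconstruction under a microscope will be judged effective only if the proportion of patients with a class III or higher biliary complication is lower in the microscopy group and the test is significant at the stated level. A significant difference in the other direction will be reported as evidence against the microscope.*

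In the same edit, state the sidedness:

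- **One-sided 5%, in favour of the microscope.** This matches the sample size. It should be described as a directional test, not just as a chi-square with a lower cut-off.
- **Two-sided 5%.** Restate the power at 79 per group as about 70 to 72%, or plan 100 per group (200 in total) to keep 80%.

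The direction clause costs one or two sentences, with no extra patients or data and essentially no loss of power. Stating a one-sided test is equally free. Only the choice to keep 80% power with a two-sided test adds patients: 200 − 158 = 42.
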